#### Outcomes

The primary outcome is the change of BMI during the 12th week after minimization. The formula for BMI is as follows:

BMI = mass (kg)/(height(m))^2^.

The BMI of all patients will be calculated at baseline; during treatment at 4, 8, and 12 weeks; and 6-week, 12-week, and 24-week follow-up [39]. The BMI reduction will be assessed by a blinded investigator from the Clinic of Nanjing University of Chinese Medicine.

The secondary outcomes are divided into objective outcomes and patient-centered outcomes. The body weight and the waist-to-hip ratio will be used as supplementary measures in combination with the BMI, and will be calculated at baseline; during treatment at 4, 8, and 12 weeks; and at 6-week, 12-week, and 24-week follow-up. In addition, TC, TG, and HDL levels also will be tested at baseline; during treatment at 4, 8, and 12 weeks to assess the metabolic changes [40]. For patient-centered outcomes, IWQOL-Lite and SF-36 are used to measure obesity-specific quality of life. The IWQOL-Lite questionnaire is a validated, obesity-specific measure, consisting of 31 items regarding the impact of obesity on physical function, self-esteem, sexual life, public distress, and work [41–43]. Patients will be asked to rank items related to obesity in 5 areas, ranging from 5 “always true” to 1 “never true”, by an independent assessor. The independent assessor will give a detailed explanation regarding every item of this questionnaire to patients before the treatment. All the patient-centered outcomes will be detected before treatment; during treatment at 4, 8, and 12 weeks; and at 6-week, 12-week, 24-week follow-up. Adverse events and serious adverse events will be recorded during the study to assess safety. By using a valid expectation questionnaire relating to acupuncture [44], participants’ expectations for acupuncture at baseline will also be assessed.

### Statistics

#### Sample size calculation

The sample size was determined prospectively as described in a previous study that used similar outcome measurements [45]. The following formula was used to estimate the sample size:$$ n=\frac{{\left({u}_{\alpha }+{u}_{\boldsymbol{\beta}}\right)}^2\kern0.5em \left( 1+ 1/k\right){\sigma}^2}{\delta^2} $$

An independent statistician will monitor the study design from the beginning of the study and take responsibility for calculating the sample size and all data. Acupuncture treatment is reported to cause a 4.84 ± 7.38 (mean ± standard deviation) kg reduction of body weight compared to lifestyle modification treatment alone, according to a previously published systematic review [12]. This study was designed to have 80 % power and a significance level of 5 % for the purpose of discriminating differences between electro-acupuncture plus lifestyle modification and lifestyle modification alone. To achieve this, 64 patients will be included in each group and a total number of 150 patients will be enrolled, allowing for a 15 % dropout rate per group.

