Acupuncture, on the other hand, originating from China and established on the framework of traditional Chinese medicine (TCM), is one of the most important alternative and complementary therapies for treating numerous diseases. While acupuncture has been practiced worldwide, the lack of high-quality clinical evidence makes acupuncture a highly controversial therapy. Based on a series of clinical studies, which showed that acupuncture at acupoints was no more effective than acupuncture at non-acupoints, some researchers have wondered whether the effect of acupuncture is only due to the placebo effect or to bias. Recently, a meta-analysis including 18,000 randomized patients in high-quality randomized control trials has manifested novel evidence that acupuncture is superior to sham acupuncture and placebo for managing chronic pain [11]. Meanwhile, a meta-analysis containing 3013 individual patients has also indicated that acupuncture can significantly reduce average body weight (95 % confidence interval (CI) of 1.72 kg (0.50–2.93 kg)) and improve obesity rates (relative risk = 2.57; 95 % CI, 1.98–3.34) compared to lifestyle modification [12]. Furthermore, the latest systematic review has shown that acupuncture is more effective than placebo or lifestyle modification to reduce body weight and has similar effects as western anti-obesity drugs but with fewer adverse effects [13]. Thus, there is an increasing tendency to use acupuncture as an adjunctive therapy based on basic lifestyle modification treatment for obesity in both western and eastern countries.

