#### Sequence generation

Patients will be randomly allocated to one of two groups in a 1:1 ratio using a minimization procedure controlled by the GCP center. Minimization is used to balance the severity of obesity, age, and gender between the two groups. The severity of obesity is divided into 4 levels, including overweight (24 ≤ BMI < 28), obesity I (28 ≤ BMI ≤ 32), obesity II (32 < BMI < 35), and obesity III (BMI ≥ 35) [26–29]. Once the severity of obesity, age, and gender of the patients are inputted in the online software, the minimization procedure will be implemented by a skilled statistician.

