#### Analysis

The primary outcome is the change of BMI during the 12th week after minimization. To determine differences between the 2 groups after 12 weeks, analysis of covariance (ANCOVA) will be used to adjust for baseline values. Because there are two primary analyses (electro-acupuncture plus lifestyle modification versus lifestyle modification alone), Bonferroni correction will be used to address multiple testing, and a significance level of 0.05 will be used.

Statistical analyses of primary and secondary outcomes will be conducted as follows. First, all the analyses will be based on the intention-to-treat (ITT) principle. All patients, who will provide baseline data, will be included in the analyses, regardless of whether or not they complete the treatment or adhere to the protocol. Data distribution is expected to be normal, and skewed distribution data will be transformed prior to analysis. The statistical hypotheses are:

H_0_: acupuncture plus lifestyle modification = lifestyle modification (null hypothesis) versus H_1_: acupuncture plus lifestyle modification ≠ lifestyle modification (alternative hypothesis).

ANCOVA will be subsequently performed on BMI, body weight, and waist-to-hip ratio data as well as SF-36 and IWQOL-Lite. SF-36 and IWQOL-Lite will be transformed to continuous variables before analysis. Missing values will be addressed using the methods of last observation carried forward (LOCF). To address the results of objective outcomes, logistic regression analysis will be used to analyze dependent variables, including TC, HDL, and TG levels. These statistical analyses will be performed using SPSS 15.0 statistics software (SPSS Inc., Chicago, IL, USA) and SAS 9.0 (SAS Institute Inc., Cary, NC, USA).

To avoid potential confounding factors, additional sensitivity analyses will be conducted following these statistical analyses by using STATA (StataCorp, College Station, TX, USA) or R methods. Patient expectations also will be included as ordinal fixed factors in the sensitivity analyses. Full analysis set and the potential confounding factors relating to baseline differences will be used to calculate the results.

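### Two irreconcilable weight effects are cited from one review, the stated 64 per group follows from neither, and 80 % power is not reached within the quoted interval at the stated SD

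*Protocol article*

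**What the plan says.** The Background of the Protocol article reports from a meta-analysis that "acupuncture can significantly reduce average body weight (95 % confidence interval (CI) of 1.72 kg (0.50–2.93 kg") when "compared to lifestyle modification [12"].

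The Sample size calculation says that acupuncture gives a "4.84 ± 7.38 (mean ± standard deviation) kg reduction of body weight compared to lifestyle modification treatment alone", "according to a previously published systematic review [12"]. It sets "80 % power and a significance level of 5" %, prints the usual two-mean formula, and arrives at 64 patients per group, raised to 150 in total for 15 % dropout.

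Allocation is equal (Sequence generation: "Patients will be randomly allocated to one of two groups in a 1:1 ratio"). The test is two-sided, since the alternative in the Analysis section is "acupuncture plus lifestyle modification ≠ lifestyle modification (alternative hypothesis"). The primary outcome in the Outcomes and Analysis sections is change in BMI at week 12. Body weight is a secondary outcome.

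**The concern.** Both sections cite one source for one outcome against a lifestyle comparator, and the numbers cannot both describe the same result: 4.84 kg lies well above the upper limit of 2.93 kg. The protocol names no subset or single trial as the origin of the larger figure and gives no reason for preferring it.

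The same paragraph has a second break. The group size and power it states do not come out of the effect and SD it states. A reader therefore cannot tell what difference the trial was sized to detect.

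At stake is the meaning of the 80 % claim. If the effect in the Background is the realistic one, a non-significant result could be quite likely, and the protocol gives no hint of that.

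**Working it through.** **Inputs.** Effect 4.84 kg and SD 7.38 kg (Sample size calculation); effect 1.72 kg, CI 0.50 to 2.93 (Background); 80 % power, 5 % level, 64 per group (Sample size calculation); two-sided (Analysis); k = 1 (Sequence generation).

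**The two effects.** 4.84 / 1.72 = 2.8, and 4.84 > 2.93.

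**The plan's own figure.** The printed formula is n = (u_α + u_β)² (1 + 1/k) σ² / δ², with (1.960 + 0.842)² = 7.849.

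- n = 7.849 × 2 × 7.38² / 4.84² = 7.849 × 2 × 54.46 / 23.43 = 36.5, so 37 per group (38 by the t-test). The stated 64 is not reproduced.
- Variants do not recover it: one-sided 5 % gives 29, a Bonferroni level of 0.025 gives 45, 90 % power gives 49, and 95 % power gives 61.

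**What 64 per group corresponds to.** Solving for δ: √(2/64) × 2.802 = 0.495 SD, or 3.65 kg at SD 7.38 kg. The t-test gives 0.50 SD, or 3.68 kg, and a standardised effect of exactly 0.5 needs 63.8 per group. The planning inputs imply 4.84 / 7.38 = 0.66 SD. So 64 matches a half-SD difference, and 3.68 kg is still above 2.93 kg.

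**Power for body weight with 64 per group, if SD 7.38 kg applies.** The standard error of the difference is 7.38 × √(2/64) = 1.305 kg, and power ≈ Φ(δ / 1.305 − 1.960).

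| δ (kg) | δ / SE | Power (normal) | Power (t-test) |
|---|---|---|---|
| 1.72 | 1.318 | 26.1 % | 25.8 % |
| 2.93 | 2.246 | 61.3 % | 60.6 % |
| 4.84 | 3.710 | 96.0 % | 95.7 % |

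At 1.72 kg, 80 % power would take 7.849 × 2 × 54.46 / 2.958 = 289 per group. This is given for scale only.

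**Dependence on the SD.** The Background gives no SD, so the following are assumed values at δ = 1.72 kg and 64 per group: SD 6 kg gives 37 %, 5 kg gives 49 %, 4 kg gives 68 %. Reaching 80 % needs an SD of about 1.72 / 0.499 = 3.45 kg.

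**Baseline adjustment.** If 7.38 kg were an unadjusted SD, ANCOVA would shrink it by √(1 − ρ²). To get to 3.45 kg, √(1 − ρ²) = 3.45 / 7.38 = 0.467, so ρ ≈ 0.88. The protocol states no correlation.

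**All 75 per group analysed.** Power at 1.72 kg is 29.7 %, and at 2.93 kg it is 68 %.

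**The case against.** Four points on the other side deserve weight.

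- *The larger figure may be legitimate.* The Background notes that many forms of acupuncture are in use, and its wording of the comparator is not identical to that in the sample-size paragraph, which adds that lifestyle modification was given alone. A confidence interval for a pooled mean does not rule out a larger effect in one trial or subset. A reader might infer that the quoted evidence excludes 4.84 kg. It does not go that far: the figure is unexplained and unreconciled, and the review itself is not at hand.
- *The SD is as uncertain as the effect.* The 26 % joins the Background effect to the SD from the disputed sentence. It is unclear whether 7.38 kg is the SD of change or something else, and the planned ANCOVA could reduce it. This stands, so the 26 % must carry its condition. It does not restore 80 % for any assumed SD from 4 to 7.38 kg, unless the gain from baseline adjustment brings the effective SD down to about 3.45 kg.
- *Body weight is not the primary outcome.* This also stands. The figures are for kilograms and cannot be read as the power for BMI change. Equally, nothing in the protocol supports 80 % for BMI change.
- *The analysis keeps every patient with baseline data.* Up to 75 per group may be analysed, but this moves the result by only a few points.

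**Conclusion.** The defect holds as an internal contradiction with two parts: two effects from one reference that are not reconciled, and a group size and power that do not follow from the stated inputs. On those inputs, 64 per group gives about 96 % power. Its 80 % point is 0.50 SD, which at SD 7.38 kg is 3.68 kg and lies beyond the upper limit of the interval in the Background.

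Power for body weight at 1.72 kg is about 26 % if SD 7.38 kg applies, and 37 to 68 % at assumed SDs of 6 down to 4 kg. These results assume 64 analysed per group, a two-sided 5 % test and no credit for baseline adjustment.

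Three stronger readings are not supported. The trial does not simply have 26 % power, since that is conditional on the SD and concerns a secondary outcome. The 80 % is not the power at 4.84 kg, since the arithmetic shows otherwise. And the protocol does not say that a null result would be taken as evidence against acupuncture, because it does not say how such a result will be read.

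**What to change.** Leave enrolment unchanged and correct the text of the Sample size calculation:

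1. Reconcile the two figures from reference 12. State which comparison, subset or trial 4.84 ± 7.38 kg comes from, why it was chosen over 1.72 kg, and what the SD measures.
2. State that 64 per group gives 80 % power, two-sided 5 %, for a difference of 0.50 SD, and remove the implication that 64 was obtained from 4.84 and 7.38 kg.
3. Report the power for body weight at 1.72 and 2.93 kg, with the SD assumption beside it and any credit for baseline adjustment shown with its assumed correlation.
4. Express the detectable difference for BMI change, the primary outcome, as 0.50 times an assumed SD of BMI change, and give that SD and its source.

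The cost is wording, plus finding an SD for BMI change. The downside is that the power shown to readers becomes less favourable.

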**Methods/Design:**

To compare the effectiveness of acupuncture plus lifestyle modification, a 2-armed, controlled trial with randomization using minimization will be conducted on 150 simple obesity and overweight patients, aged 18–50 years, for a 36-week study duration. All patients will be randomly assigned to one of two groups and will receive either acupuncture plus lifestyle modification or lifestyle modification alone. Outcomes will be evaluated at baseline and at 4 weeks, 8 weeks, and 12 weeks during treatment as well as at 6-week, 12-week, and 24-week follow-up. The primary endpoint is change of body mass index (BMI) during the 12th week. Secondary endpoints are body weight; waist-to-hip ratio; biochemical tests including serum cholesterol (TC), triglyceride (TG) and high-density lipoprotein (HDL) levels; and answers to the Short Form 36 (SF-36) and the Impact of Weight on Quality of Life Questionnaire-Lite Version (IWQOL-Lite). Statistical analyses will be based on the intention-to-treat (ITT) principle. The main endpoint will be analyzed by analysis of covariance (ANCOVA), and the objective outcome results will be analyzed by logistic regression analysis. To avoid potential confounding factors, additional sensitivity analyses will be conducted following these statistical analyses.

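### The sample size is justified with a body-weight effect although the primary test is of BMI change, and on those inputs the stated 80 % is not the power on either scale

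*Protocol article*

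**What the plan says.** The Outcomes section of the protocol article fixes the primary endpoint: "The primary outcome is the change of BMI during the 12th week after minimization". The Analysis section repeats it and names the test: "analysis of covariance (ANCOVA) will be used to adjust for baseline values".

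Body weight has a lower rank. The abstract states: "Secondary endpoints are body weight; waist-to-hip ratio". The Outcomes section agrees: "The body weight and the waist-to-hip ratio will be used as supplementary measures in combination with the BMI".

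The Sample size calculation section gives a two-mean formula without covariate adjustment and one pair of inputs, a mean of 4.84 with SD 7.38, described as a "kg reduction of body weight compared to lifestyle modification treatment alone, according to a previously published systematic review". The design values are "80 % power and a significance level of 5" per cent. From these the section arrives at 64 per group, and at 150 in total after allowing for 15 % dropout. It also refers to a previous study with similar outcome measures. It states no difference in kg/m², no SD of BMI change and no correlation between baseline and follow-up BMI.

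**The concern.** A power statement should describe the test on which the trial will be judged. Here the endpoint that is sized (body weight in kg) and the endpoint that is tested (BMI change in kg/m²) differ, and the article neither converts one to the other nor argues that they are interchangeable. Two things are at stake.

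- The 80 % is a headline design figure that readers will attach to the primary test, and the article does not show it for that test.
- With no target BMI difference on record, a non-significant or small BMI result cannot be set against the effect that the trial was built to detect.

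The kg inputs also do not lead to the sample size printed beside them, so the 80 % cannot simply be read as the power for body weight.

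**Working it through.** **Inputs from the article.** δ = 4.84 kg, σ = 7.38 kg, α = 0.05, power 80 %, 64 per group, 15 % dropout (Sample size calculation). Allocation is 1:1, so k = 1 (Sequence generation). The test is two-sided, because the alternative hypothesis is one of inequality (Study design; Analysis). BMI = mass / height² (Outcomes).

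**Step 1: the article's own figure.** The formula is n = (u_α + u_β)² (1 + 1/k) σ² / δ².

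- (1.960 + 0.842)² = 7.849, and multiplied by 2 this is 15.70
- σ²/δ² = (7.38/4.84)² = 2.325
- n = 15.70 × 2.325 = 36.5, so **37 per group, not 64**

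Variants do not recover 64 at 80 % power:

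| Variant | n per group |
|---|---|
| Two-sided 5 %, t-test | 38 |
| One-sided 5 % | 29 |
| Two-sided 2.5 % (Bonferroni for two tests) | 45 |
| Two-sided 5 %, 90 % power | 49 |
| Two-sided 5 %, 95 % power | 61 |

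The dropout step is consistent with 64: 128/0.85 = 150.6, against 150 stated.

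**Step 2: power for body weight at 64 per group.** The standardised effect is 4.84/7.38 = 0.656. Then 0.656/√(2/64) = 3.71, and 3.71 − 1.96 = 1.75, so power is about **96 %**. At two-sided 2.5 % it is about 93 %.

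**Step 3: what 64 per group at 80 % corresponds to.** The detectable standardised difference is 2.802 × √(2/64) = 0.495 (0.499 with the t-test), or about 0.50 SD. On the kg scale that is 3.65 kg with SD 7.38 kg, or 4.84 kg with SD 9.77 kg. Neither pair is in the article.

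**Step 4: conversion to BMI.** The article gives no heights, so these are assumed.

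| Assumed height | 4.84 kg as kg/m² | 7.38 kg as kg/m² | Ratio |
|---|---|---|---|
| 1.60 m | 1.89 | 2.88 | 0.656 |
| 1.65 m | 1.78 | 2.71 | 0.656 |
| 1.70 m | 1.67 | 2.55 | 0.656 |

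At a single height the ratio does not change, so n stays at 37 and power at 64 per group stays at about 96 %.

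Heights vary between patients, so this was also simulated: mean height 1.65 m, height SD 0.06, 0.08 or 0.09 m, weight changes drawn with the article's δ and σ, unadjusted t-test, 20,000 replicates. Power for BMI change was 95.9, 95.5 and 95.4 %, against 95.9, 95.7 and 95.7 % for weight change.

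**Step 5: the missing target.** If 7.38 kg did represent the SD of weight change, 0.50 SD would be about 1.35 kg/m² at 1.65 m (0.499 × 2.71). This is illustrative only, because the article gives no SD of BMI change.

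**The case against.** The strongest reply is that weight is a near-perfect proxy for BMI here. Adult height does not change over 12 weeks, so each patient's BMI change is the weight change divided by a constant, and the Aims section names both measures. Steps 2 and 4 bear this out: the standardised effect carries over almost unchanged. Sizing with an unadjusted formula and analysing with baseline adjustment is also common and generally does not cost power. A journal article may leave detailed inputs to the full protocol. All of this stands, and it removes any claim that the choice of scale harmed the trial.

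It does not rescue the stated figure. If the two scales are equivalent, the printed inputs imply 37 per group, or about 96 % power at 64, on both. The article also did more than omit an input: it printed a basis, on an endpoint other than the primary one, that does not give the printed result.

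A reader might infer that the trial is underpowered for BMI. The documents do not support this, since their own inputs point to more than 80 %. Low power appears only if the effect itself is replaced. The Background quotes 1.72 kg (0.50-2.93) against lifestyle modification from the same systematic review. With SD 7.38 kg and 64 per group, that effect has about 26 % power, but it does so for body weight itself. This is a separate question about which effect was taken from the review, and it does not follow from the endpoint mismatch.

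A reader might also infer that 64 was calculated from the kg figures and merely attached to the wrong endpoint. Step 1 rules that out for the formula as printed.

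**Conclusion.** The point holds in a limited form. The 80 % power is not shown for the primary ANCOVA of 12-week BMI change, because the only effect and SD given are for a secondary outcome and no BMI target or SD is stated. On those inputs 80 % is not the power for either scale: the formula gives 37 per group, and 64 per group gives about 96 % for weight and about 95-96 % for BMI. As it stands, 64 per group at 80 % means a difference of about 0.50 SD, which the article never states.

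The BMI figures assume heights averaging about 1.65 m and that 7.38 kg is the within-group SD of weight change. The article does not say which SD it is. If the SD of BMI change in this trial, relative to the true effect, differs from that, the power differs in either direction. The defect is therefore a power statement that needs correcting, not evidence of an inadequate sample size.

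**What to change.** Keep 64 per group and rewrite the justification for the primary endpoint:

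1. State that 64 per group gives 80 % power at two-sided 5 % for a between-group difference of 0.50 SD in 12-week BMI change.
2. Give the target difference in kg/m² and the assumed SD of BMI change, each with its source. The 0.50 SD is what the chosen number can detect, so the target needs its own justification. If the sourced target is smaller than 0.50 SD, say what power 64 per group then gives.
3. Remove the 4.84 and 7.38 kg figures or correct them. They should not be kept as a supporting calculation, because they yield 37.
4. If the 1.72 kg effect from the Background is discussed, present it as a separate sensitivity to the effect assumption.

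The cost is wording in the Sample size calculation section. Patient numbers, visits and the planned analysis do not change, which suits a trial that is already recruiting. The restated power may be higher or lower than 80 %, depending on the BMI inputs that can be sourced.

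### The printed formula and inputs give 37 patients per group, not 64, so the stated sample size and the stated 80 % power do not belong together

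*Protocol article*

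**What the plan says.** All the planning figures stand together under Sample size calculation in the protocol article. The section introduces its formula with "The following formula was used to estimate the sample size" and prints

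n = (u_α + u_β)² (1 + 1/k) σ² / δ².

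The only effect and spread given are from a systematic review: "Acupuncture treatment is reported to cause a 4.84 ± 7.38 (mean ± standard deviation) kg reduction of body weight", relative to lifestyle modification alone. Power is set at 80 % and significance at 5 %. The section presents the result as what is needed to meet those targets: "64 patients will be included in each group and a total number of 150 patients will be enrolled", the larger figure allowing for 15 % dropout per group.

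Two further inputs come from other sections. Sequence generation gives 1:1 allocation. Study design and Analysis both state an alternative hypothesis of inequality, which is two-sided.

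**The concern.** A formula, its inputs and its result are all printed, so the result should follow. A standardised difference of 4.84/7.38 = 0.656 is well above 0.50, yet 64 per group is the familiar answer for 0.50 at two-sided 5 % and 80 % power.

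If the figures do not agree, the article does not say what the trial was designed to detect. The difference could be 4.84 kg at much more than 80 % power, a smaller difference at 80 % power, or something based on inputs that were not printed. A null result in particular cannot then be read against a known detectable difference. The section also says the size follows an earlier study with similar outcomes but takes its effect from the review. That is not an error in itself, but it makes the origin of 64 harder to trace.

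**Working it through.** **Inputs**

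| Quantity | Value | Source |
|---|---|---|
| δ | 4.84 kg | Sample size calculation |
| σ | 7.38 kg | Sample size calculation |
| Power | 80 % (u_β = 0.842) | Sample size calculation |
| Significance | 5 %, two-sided (u = 1.960) | Sample size calculation; sidedness from the hypotheses in Study design and Analysis |
| k | 1 | Sequence generation (1:1) |
| Dropout | 15 % | Sample size calculation |

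**Step 1: attempt to reproduce 64**

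n = (1.960 + 0.842)² × 2 × 7.38² / 4.84² = 36.5, so **37 per group**. A t-test calculation gives 37.5, so 38. The stated 64 is 64/37 = 1.73 times the formula's answer, or 73 % larger.

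**Step 2: other readings of the same inputs (normal formula, per group)**

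| Significance | 80 % power | 90 % power | 95 % power |
|---|---|---|---|
| One-sided 5 % | 29 | 40 | 51 |
| Two-sided 5 % | 37 | 49 | 61 |
| Two-sided 2.5 % | 45 | 58 | 71 |
| Two-sided 1 % | 55 | 70 | 83 |

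The 2.5 % row is included because the Analysis section says "Bonferroni correction will be used to address multiple testing, and a significance level of 0.05 will be used". The nearest entry to 64 is 61 (62 by t-test), which would need 95 % power and so contradicts the stated 80 %. At two-sided 5 % and 80 % power, changing k to 0.5 or 2 gives 55 or 28, and inflating the SD by √2 gives 73. None of these is 64.

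**Step 3: the dropout step**

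64/0.85 = 75.3. Strict rounding up gives 76 per group, 152 in total. The stated 150 is 75 per group, and 75 × 0.85 = 63.75. This is close enough, and it confirms that 64 is the figure before dropout. The break lies between the inputs and 64.

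**Step 4: what 64 per group delivers**

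- Power at δ = 4.84 kg, σ = 7.38 kg: 0.656 × √(64/2) = 3.710, and 3.710 − 1.960 = 1.750, so power is Φ(1.750) = 96.0 %. The t-test gives 95.7 %. At a significance level of 2.5 % it is 92.9 %.
- Detectable difference at two-sided 5 % and 80 % power: by t-test 0.499 SD, and 0.499 × 7.38 = 3.68 kg. The printed normal formula gives 2.802 × 7.38 × √(2/64) = 3.65 kg.
- SD that would make 4.84 kg need 64 per group: 4.84 / (2.802 × √(2/64)) = 9.77 kg.

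**Step 5: a possible origin**

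A t-test calculation at a standardised difference of 0.50 gives 63.8, so exactly 64 (62.8, so 63, by the printed formula). The article never states 0.50, so this is a conjecture.

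**The case against.** The strongest reply is that the discrepancy is harmless. On the printed inputs the trial is larger than it needs to be, the correction changes no endpoint, test or enrolment, and the final result will be judged by its estimate and confidence interval. The direction is indeed conservative, and the estimate and interval do not depend on the planning figures. The reassurance holds only if 4.84 and 7.38 kg are the true inputs, which the contradiction puts in doubt. The Background section cites the same review for a reduction of 1.72 kg (0.50 to 2.93) against lifestyle modification. The two figures may come from different comparisons; the article does not say. For illustration, assuming SD 7.38 kg, 1.72 kg gives 1.72/7.38 × √32 − 1.960 = −0.64, which is about 26 % power at 64 per group.

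It can also be said that 4.84 and 7.38 are not labelled δ and σ, and that the section leaves k and sidedness unstated. That is true, but they are the only effect and spread offered, and the other choices of k and sidedness tried in Step 2 do not give 64 either.

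A third reply is that an input was simply mistyped: an SD near 9.8 kg would fit 64. That is possible, and it is a reason to ask the sponsor which inputs were used. It does not rescue the text as printed.

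Nor is this a detail left to a fuller document. Nothing is missing; the printed figures disagree with each other.

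**Conclusion.** The sample size statement is wrong as written. Its formula, effect, SD, significance level and power give 37 per group (38 by t-test), against a stated 64. Equivalently, 64 per group carries about 96 % power on those inputs, or 80 % power for 0.50 SD (3.68 kg at SD 7.38 kg).

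This rests on reading 4.84 and 7.38 kg as the difference and its SD, on 1:1 allocation, and on a two-sided test. The last two are stated elsewhere in the article. The printed inputs do not imply an underpowered trial, but the article gives no secure basis for saying what the trial is powered to detect. The calculation is in kilograms while the primary outcome is change in BMI; that is a separate matter, and this conclusion does not depend on it.

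**What to change.** Keep 64 per group and 150 in total. The sponsor should first establish which inputs produced 64, and then correct the paragraph in one of two ways:

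- **(a)** State that 64 per group gives 80 % power at two-sided 5 % for a standardised difference of 0.50, equal to 3.68 kg if the SD is 7.38 kg. Say that this is a t-test calculation, since the printed normal formula gives 63 for 0.50.
- **(b)** If 4.84 and 7.38 kg are confirmed as the intended inputs, keep them and restate the power at 64 per group as about 96 % at two-sided 5 %.

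If an input proves to have been misprinted, print the correct value and show that it returns 64. In every case write the formula with u_(α/2), so that it matches the two-sided hypothesis.

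The cost is one paragraph of protocol wording with no change in enrolment. The article reports that recruitment is under way, so the correction should be dated and documented before results are known.
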